## Abstract

**Background:**

Despite the high prevalence of lower urinary tract symptoms (LUTS) in patients with Parkinson's disease (PD)—ranging from 27 % to 85 % including symptoms such as urinary urgency,- incontinence, frequency, and nocturia—evidence-based treatment options remain limited. Conservative treatments, such as bladder training, pelvic floor muscle exercises (PFME) with biofeedback and electrical stimulation, have been shown safe and effective in the general population, with minimal side effects. However, their efficacy specifically in PD patients remains unclear. Therefore this study aims to evaluate the effect of electrical stimulation with conservative treatment for LUTS in PD patients.

**Methods and analysis:**

This randomized controlled trial includes three study arms. All three groups will receive conservative treatment in combination with different electrical stimulation parameters, small- and broad pulse duration and sham electrical stimulation. In total 150 PD patients with self-reported LUTS who are able to attend a pelvic physical therapy practice independently and complete online questionnaires will be enrolled. The primary outcome is the difference in international prostate symptom score (IPSS), with a range of 0–35.

A minimal important difference of 4.2 between baseline and 12 weeks of treatment will be statistical significant (p˂0.05). Secondary outcome include questionnaires evaluating bladder dysfunction, burden, and quality of life and will be collected at baseline, 12 weeks and 24 weeks and at one year. Additionally pelvic floor muscle function will be assed at baseline and after 12 weeks.

All participants receive eight sessions along with their assigned electrical stimulation treatment and conservative treatment.

## Introduction

1

Parkinson's disease (PD) is one of the fastest growing neurodegenerative disorders. It is estimated that PD affects 1 % of the population over the age of 60 years [1,2]. PD comprises a variety of motor symptoms and a wide range of non-motor symptoms (NMS), including several autonomic dysfunctions, which accumulate as the disease progresses. Lower urinary tract symptoms (LUTS) are reported in 27–85 % of PD patients, can occur early in the disease, 50 % at onset, and have a significant impact on the quality of life (QoL) of patients [[3], [4], [5], [6], [7], [8], [9]].

LUTS are divided into three groups, storage, voiding and postmicturition symptoms [10]. Both central cortical areas and peripheral nerves in the pelvis regulate the urinary bladder and bladder outlet [11]. Although the exact pathophysiology remains unclear, LUTS in PD are believed to have a multifactorial origin, reflecting the widespread involvement of multiple areas within the nervous system [12].

The majority of PD patients experience storage symptoms (formerly known as irritative symptoms) such as nocturia, the need to urinate more than once per night (57–86 %), urinary frequency (32–71 %), urinary urgency (UU) (32–68 %) and urgency urinary incontinence (UUI) (21–40 %) [4,8,13,14]. Symptom prevalence is significantly higher in PD patients than in the general population [4,15,16]. LUTS increases with the progression of PD and may lead to early admission into care and an increase of health related cost [12]. Additionally, LUTS exerts a profound influence on health-related QoL even in patients who have only recently been diagnosed [17,18]. In general, LUTS and the associated fear of urinary incontinence have a limiting effect on daily activities and may act as a barrier to exercise and sports participation [19]. A significant association has been observed between these symptoms and an increased risk of falls [20].

According to clinical guidelines, treatment of LUTS in general population consists of conservative therapy and medication such as antimuscarinics and β-3-adrenergic receptor-agonist [12,21]. Conservative treatment may hold component such as behavioral advice, bladder training, pelvic floor muscle exercises (PFME) with or without biofeedback and electrical stimulation (ES) [22,23]. Antimuscarinic agents have proven to be effective in alleviating LUTS in general population. However in PD patients these drugs are less effective, less well tolerated, and have more serious side effects like constipation, cognitive decline and xerostomia [[24], [25], [26]]. Current guidelines for the management and treatment of LUTS in PD scarcely mention conservative therapy as an option, due to a lack of powered randomized controlled trials [20,27]. Some smaller studies show promising results such as significant improvements in voided volume and reduction in number of voids, for bladder training and PFME with biofeedback in patients with PD [28,29]. Biofeedback can be provided with electromyography (EMG), using an intra vaginal- or anal probe. EMG measures electrical activity of the pelvic floor muscles (PFM) and provides visual feedback to help patients learn to contract these muscles effectively and suppress UU [29]. The major advantage of this form of therapy is the absence of side effects.

Neuromodulation can also be applied to reduce UU and UUI. The mechanism of neuromodulation, to reduce UU, is hypothesized to involve the reflex inhibition of detrusor contractions through activation of afferent fibers of the pudendal nerve and sacral cord. **Afferent fibers can be stimulated via the pudendal nerve**, **sacral nerve roots (S3 and S4) or other peripheral nerves corresponding to these roots** [23]. Neuromodulation can be applied in several ways, including surface electrodes, like transcutaneous tibial nerve stimulation (TTNS), needle electrodes such as percutaneous tibial nerve stimulation (PTNS) and implanted wire electrodes, i.e. sacral neuromodulation (SNM).

In a small number of studies, PTNS and TTNS have demonstrated potential benefits in reducing UU in PD, however there is uncertainty regarding long-term effects [[30], [31], [32]]. SNM shows promising results, but research on its use for PD patients is still limited and the number of patients studies is small [33].

Add-on ES, to conservative therapy with the same intra vaginal- or anal probe, to reduce UU could be of interest and might be beneficial in PD. The treatment is well-tolerated by patients in the general population, has a short duration and is not expected to cause serious adverse effects [34].

In general, when using ES for neuromodulation, there is a lack of knowledge regarding the optimal parameters for its use [23]. Frequency is typically set at a relatively low rate, below 20 Hz, while the pulse duration varies across a broad spectrum, ranging from 100 to 1000 μs [23,35,36].

Given this knowledge gap, the primary objective of this study is to evaluate the effectiveness of ES, using two distinct electrical stimulation -one with a short pulse duration and one with a broad pulse duration-compared to sham stimulation together with PFME and biofeedback in reducing LUTS in PD.

## Methods

2

### Trial design

2.1

This is a monocenter three-armed randomized controlled trial (RCT). All participants receive bladder training and PFME with biofeedback. In three groups the efficacy of two different active parameters of ES are compared with sham ES.

The three study arms are:

Group 1: ES with phase duration 200μs, frequency 20hz, 20 min continuous mode, active electrodes on the ventral side of the probe;

Group 2: ES with phase duration 1000μs, frequency 8hz, 20 min continues mode, active electrodes on the ventral side of the probe;

Group 3: ES with phase duration 200μs, frequency 100hz, 20 min intermittent mode: with 2 s of active ES and 20 s no stimulation, with active electrodes on the dorsal side of the probe, sham ES. (control group).

### Participants: eligibility and recruitment

2.2

Inclusion criteria are: Parkinson's disease, ≥18 years of age, self-reported LUTS, stable Parkinson's and/or bladder medication for at least three months, including alpha-blocker medications, sufficient understanding of the Dutch language, able and willing to independently read and fill in online questionnaires, able to independently visit a pelvic physical therapy practice.

Exclusion criteria are: other neurological diseases, surgery in the pelvic region in the last year, cancer or cancer treatment in the pelvic region, pregnancy, current urinary tract infection, pure stress urinary incontinence without urinary-urgency, -frequency, nocturia, Botulinum toxin treatment, PTNS or pelvic physical therapy in the last year, sacral neuromodulator, pacemaker and implantable cardioverter defibrillator (ICD), Deep Brain stimulation (DBS).

Participants are recruited through advertisement on the website of the Dutch Parkinson association and the Dutch brain association, with flyers in physical therapy practices, and by presentations for small local patient groups. Potential participants can register for the study, without the intervention of a healthcare provider.

Neurologists, urologists, and the PD nurse at LUMC, Maastricht University Medical Center (MUMC+), and Alrijne hospital (Leiden) inform potential participants about the study and provide informational leaflets.

### Outcome measures

2.3

#### Questionnaires

2.3.1

Questionnaires (Table 1) will be sent to the participant online at T0, T1 (12 weeks), T2 (24 weeks), and T3 (one year).•The International Prostate Symptom Score (IPSS), validated for use in both men and women [37,38]. This questionnaire is a standard tool for assessing Lower Urinary Tract Symptoms (LUTS) in the general population. Although it is not validated in PD, it is the only questionnaire that has been referenced in existing research related to PD, providing some relevant context for this population [3,6,39]. It contains 7 items on storage of urine and micturition and is scored on a 6 point scale. An 8th, separate question assesses QoL and will not be added to the score. The total score on questions 1–7 lies between: 0–35 points. The higher the score, the more severe the symptoms in which a score between 0 and 7 points is interpreted as mild symptoms, a score between 8 and 19 points as moderate symptoms and a score between 20 and 35 points as severe symptoms [40].•The International Consultation on Incontinence Questionnaire-Urinary Incontinence Short form (ICIQ-UI SF), evaluating four questions about frequency, urinary incontinence and amount of leakage and overall impact of urinary incontinence. The score ranges from 0 to 21 points with greater values indicating increased symptom severity, level of evidence is grade A [41].•The International Consultation on Incontinence Questionnaire-Lower Urinary Tract Symptoms quality of Life (ICIQ-LUTSqol). It provides a measure to assess the impact of urinary incontinence on QoL with particular reference to social effects level. The score ranges from 19 to 76 points with higher values indicating increased impact on QoL.The amount of bother is measured on a 0–10 point Likert scale. They are not incorporated in the overall score but indicate impact of individual symptoms for the patient, level of evidence grade A [42].•The International Consultation on Incontinence Questionnaire-Overactive Bladder (ICIQ-OAB), for questions evaluating UU with and without urinary incontinence, associated with frequency and nocturia. The score ranges from 0 to 16 points with higher values indicating increased symptom severity. The ICIQ-OAB is validated in Dutch, level of evidence grade A [43,44].

**Table 1 tbl1:** Summary of questionnaires and pelvic floor muscle assessment.

Assessment schedule	T0 baseline	T1 12 weeks	T2 24 weeks	T3 1 year
Baseline characteristics	X			
IPSS	X	X	X	X
ICIQ-UI SF	X	X	X	X
ICIQ-LUTSqol	X	X	X	X
ICIQ-OAB	X	X	X	X
GPE		X		
24 h bladder diary	X	X		
Pelvic floor muscle assessment	X	X		

IPSS=International Prostate Symptom Score, ICIQ-UI SF=International consultation on Incontinence- Urinary Incontinence Short Form, ICIQ-LUTSqol = International Consultation on Incontinence Questionnaire-Lower Urinary Tract Symptoms quality of life, ICIQ-OAB=International Consultation on Incontinence Questionnaire Overactive Bladder, GPE = Global Perceived Effect.

Outcome measures (table 1) assessed at inclusion (T0) and at 12 weeks (T1).•The 24 h bladder diary [45], records time of:omicturition: bladder volume (ml) and frequency,orate of UUoleakage of urineonumber of drinks: every time how much (amount in ml)•The PFM-assessment: according to International Continence society (ICS) [46].oPFM palpation: tone at rest, maximum voluntary contractions (MVC), endurance contractions (EC), co-reflex-contractionsoEMG assessment: tone at rest, 10 MVC's, 3 EC.

Outcome measure (table 1) assessed at 12 weeks (T1).•Global Perceived Effect (GPE), to quantify the patient's perceived improvement or deterioration over time, (T1), measured on a 7 point scale [47].

### Pelvic floor muscle assessment

2.4

Participants will be asked to perform a PFM contraction without contraction of surrounding (gluteal, abdominal) muscles. Initially, no instructions will be given on how to perform a PFM contraction. In case of absence, no proper contraction or co-contraction, the pelvic physical therapist (PPT) will provide clear instructions on how to perform a correct PFM contraction.

Assessment of the PFM, per vaginum/anum, consists of.•Muscle tone of m.levator ani and external anal sphincter.•PFM strength: three MVC's and three EC's•Repeatability of 10 fast contractions•Direction of pelvic floor movement: elevation, no change, descent•Relaxation post contractions: yes; partial or delayed; no, absent•Co-ordination: PFM contraction before a cough: present, absent or paradoxical contraction•Co-contractions: yes: abdominal, gluteal or no: absent

According to the terminology for PFM assessment by Frawley et all [46].

EMG assessment will be performed with the Multi Array Probe Leiden (MAPLe). The MAPLe® is a monopolar cylindrical-shaped validated probe (length 65 mm, diameter 15 mm) with 24 electrodes. It is capable of registering EMG activity nearest to the individual muscles of the PFM on the four different sides and depths [26].

The probe will be placed intra-vaginally or intra-anally with a reference electrode on the anterior superior iliac spine. Participants will be asked to perform three consecutive tasks.1.One minute rest to register baseline muscle activity. Participants will be instructed not to speak during the measurement and breathe calmly.2.Ten MVC's. Participants will be instructed to perform a controlled MVC the PFM, without co-contractions (mean and peak amplitude will be measured).3.Three EC's. The participants will be instructed to contract the PFM at such level that they can hold for 30 s (mean and peak amplitude will be measured).

### Routing and study procedures

2.5

Interested PD patients are encouraged to contact the principal investigator (PI) by phone or email. The PI will provide the patient with detailed information, both verbally and in writing. The patient will have the opportunity to ask questions and receive additional information throughout the enrolment process.

The PI verifies eligibility criteria are met (Fig. 1). If the participant is eligible, the research information sheet, two informed consent forms, a reimbursement form, and a return envelope are sent to the interested PD patient. Once both signed informed consent forms have been returned, the patient will be included (Fig. 1). The PI will sign both informed consent forms, return one to the participant, and securely store the other in a locked cabinet. All included participants will receive a reimbursement of €50. Finally, demographic data and participant characteristics will be registered.

**Fig. 1 fig1:**
[figure not shown]
Study design flow diagram LUTS: lower urinary tract symptoms; IPSS: international Prostate symptom score; ICIQ-UI SF: International Consultation on Incontinence Questionnaire urinary incontinence short form; ICIQ-LUTS-qol: International Consultation on Incontinence Questionnaire Lower urinary tract symptoms quality of live; ICIQ-OAB: International Consultation on Incontinence Questionnaire Overactive Bladder; BD: bladder diary; A-PPT: Assessment Pelvic Physical Therapist; ES: electrical stimulation; PFME: pelvic floor muscle exercise.

Data will be stored and managed in a secured online database system Castor EDC (www.castoredc.com).

At baseline (T0) and post-treatment T1) the participant will complete online questionnaires and undergo a PFM assessment (Table 1).

The PFM assessments will be carried out by one of the six assessment(A)-PPT at six sites across The Netherlands. These six A-PPTs are experienced in scientific research and have a Master's degree in Pelvic Physical Therapy [48].

The pelvic physical therapy intervention, largely based on usual care Pelvic Physical Therapy, will be provided by a protocol trained local PPT (L-PPT) close to the participants' home address. The PI has a list of protocol trained L-PPT's that can be contacted. In exceptional cases the A-PPT and the L-PPT is the same person.

The PI oversees the organization of the project and ensures that the A-PPT and L-PPT receive the required information.

After inclusion the A-PPT will make two appointments (T0 and T1) with the participant, with a 12 weeks interval.

The PFM assessment will consist of a standardized protocol: digital palpation per vaginum/rectum and an EMG assessment of the PFM [46]. The A-PPT is responsible for entering data of the PFM assessment and bladder diary in the Castor database.

After baseline assessment, participants will be randomly assigned in blocks with a computer generated program Castor EDC (www.castoredc.com). Participants will be stratified by gender and allocated (1:1:1) into one of the three study arms (Block size vary between 6,9,12). The randomization codes are software generated before start of the intervention. The PI has no influence on the randomization process.

Communication between PI, A-PPT's and L-PPT's will be via a secure app and email.

The two appointments with the A-PPT are funded by the grant, while the treatment is covered by basic healthcare insurance.

The personal probe used for EMG assessment and ES will be provided free of charge.

Participants may withdraw from the study at any time for any reason, without consequences. The research team may decide to withdraw a subject from the study for urgent medical reasons.

### Intervention and blinding

2.6

The intervention consists of eight protocol-based treatment sessions of 30 min each over a period of 10–12 week. The protocol consists, for all participants, of bladder training [22], biofeedback assisted PFME, MVC's and endurance contractions according to the (dys)function of the PFM and the ability of the individual participant. It also includes relaxation and coordination exercises of the PFM combined with abdominal breathing. Visual feedback of the EMG signals with verbal instruction and reinforcement will be used to teach participants how to control the PFM and how to use the PFM for urge suppression techniques.

For urge suppression, the mean of the peak values of the 10 MVCs obtained during the EMG assessment is used. Half of this mean is displayed as a reference red, top line on the screen, providing visual feedback to both the participant and the therapist. Another red, bottom line, representing the mean baseline muscle activity from the EMG assessment, is used for relaxation. During the intervention, the red line will be adjusted in case of increasing PFM activity in MVC's and decreasing activity in case of more relaxation.

ES will be applied for 20 min, in six therapy sessions.

Participants will have to exercise (approximately 10 min per day) at home in between sessions and learn to integrate the techniques in case of UU and into their daily activities.

Participants are blinded for the treatment, but blinding is impossible for the A- and L-PPT's. Data analysis is conducted by both researcher and statistician, with the statistician being fully blinded.

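### Section 2.6 calls blinding of the assessing therapists impossible, but section 2.5 has them normally only assess; T1 palpation ratings are left open to avoidable assessor bias

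*Protocol article*

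**What the plan says.** Section 2.6 (Intervention and blinding) deals with both kinds of therapist in one sentence: "Participants are blinded for the treatment, but blinding is impossible for the A- and L-PPT's". It gives no separate explanation for the A-PPT.

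Section 2.5 (Routing and study procedures) separates the roles:

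- Assessment: "The PFM assessments will be carried out by one of the six assessment(A)-PPT at six sites across The Netherlands".
- Treatment: the intervention "will be provided by a protocol trained local PPT (L-PPT) close to the participants' home address".
- Overlap: "In exceptional cases the A-PPT and the L-PPT is the same person". The number of such cases is not given.
- Visits: "After inclusion the A-PPT will make two appointments (T0 and T1) with the participant, with a 12 weeks interval".
- Allocation: "After baseline assessment, participants will be randomly assigned in blocks with a computer generated program Castor EDC".
- Data entry: "The A-PPT is responsible for entering data of the PFM assessment and bladder diary in the Castor database".

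The same section says that the principal investigator, the A-PPTs and the L-PPTs communicate through a shared app and email. The article describes no step that keeps the arm from the A-PPT. Section 3.1 lists pelvic floor muscle function (palpation and EMG) and the bladder diary as secondary outcomes. Table 1 schedules them at T0 and T1 only.

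**The concern.** A therapist who sets the stimulation parameters and electrode side must know the arm. A therapist who only examines the participant before and after treatment usually need not. The article extends to all six assessors a constraint that, on its own description of the roles, binds only the treating therapist and the few people who do both jobs.

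Palpation is at stake. Section 2.4 has the assessor grade muscle tone, strength, direction of movement, completeness of relaxation, co-ordination before a cough and co-contraction. The assessor also decides whether a contraction is correct, and so whether instruction is given. These are judgements by hand and eye, which knowledge of the arm can influence. T1 is their only post-treatment measurement, so no later assessment could show or correct a distortion.

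**Working it through.** The article gives no figure on this point, so the check sets its own statements side by side.

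**1. Could the A-PPT know the arm at T0?** No. Section 2.5 places randomisation after the baseline assessment. Only T1 is exposed.

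**2. Does the A-PPT deliver stimulation?** Normally not. Section 2.5 gives treatment to the L-PPT, and section 2.6 places stimulation in six therapy sessions. The assessment visits described in sections 2.4 and 2.5 contain palpation and EMG recording but no stimulation.

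**3. Do the described A-PPT tasks differ by arm?** No. Palpation, the three EMG tasks (rest, ten maximal contractions, three endurance contractions) and data entry are the same for all participants. The EMG values that set the biofeedback reference lines (section 2.6) pass from assessment to therapy, so they do not require the assessor to know the arm.

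**4. Where is blinding truly impossible?** For the L-PPT, and where A-PPT and L-PPT coincide. Section 2.5 calls the latter exceptional.

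**5. Which outcomes are exposed, and how much?**

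- *Palpation at T1:* clearly exposed, because the assessor makes the rating.
- *EMG at T1:* less exposed. The probe records the amplitudes during fixed tasks under a standardised protocol. The tasks are still voluntary efforts made on the assessor's instruction.
- *Bladder diary at T1:* less exposed. It holds times, volumes and counts, and the A-PPT's stated role is data entry, so the risk is one of transcription or interpretation.
- *IPSS (primary), the ICIQ questionnaires and the perceived-effect rating:* not assessor-rated. Section 2.3.1 has the questionnaires sent to the participant online, and section 2.6 describes the participant as blinded.

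**6. How many participants?** The article plans 40 per group for analysis and 20 % loss: 40 / (1 − 0.20) = 50 per group, and 3 × 50 = 150 recruited, as stated. About 3 × 40 = 120 would then supply T1 data. How many T1 assessments have been made unmasked, and how many involve a shared therapist, cannot be derived from the article.

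**The case against.** The strongest reply is that the article is a condensed account and an operational reason may exist. It does not say who carries out the randomisation in Castor after the baseline visit, it says only that therapists receive the information they require, and the flow diagram is not available here. That stands as far as it goes: it cannot be claimed that the A-PPT never needs the arm. But the article makes a positive statement of impossibility that its own description of the roles does not support. If a reason exists, it should be stated.

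A participant might also reveal the stimulation received, since sham differs in mode, frequency and electrode side. That calls for a non-disclosure instruction. It does not make masking impossible.

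Timing and travel are fair objections. Recruitment began in September 2023 and was expected to end around August 2025 (Trial status), so a change now would mix masked and unmasked T1 assessments. The Discussion already names travel to the six assessors as a limitation. The remedy must therefore be prospective and flexible.

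A reader might infer three stronger claims that the documents do not support:

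- *That bias would favour active stimulation.* The Introduction gives the mechanism as reflex inhibition of the detrusor, and all arms receive the same muscle exercises. No direction between arms is stated for tone, strength or relaxation.
- *That all T1 muscle and diary results are biased.* The text supports only that they could be, and to differing degrees.
- *That the researcher analyses with the arms known.* Section 2.6 says: "Data analysis is conducted by both researcher and statistician, with the statistician being fully blinded". The contrast may suggest this but does not state it, and masking of analysts is commonly specified in a statistical analysis plan, which is not shown. It forms no part of this point.

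**Conclusion.** The point holds as a limited one about secondary outcomes. The article declares impossible something that its own division of roles appears to allow in all but exceptional cases, and so leaves the T1 palpation ratings open to assessor bias that could be avoided at little cost. The primary IPSS comparison and the sample size are untouched.

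The size and direction of any bias cannot be determined from the article. The conclusion assumes that the roles work as section 2.5 describes and that no undisclosed task obliges the A-PPT to know the arm.

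**What to change.** 1. Amend section 2.6 to say that L-PPTs cannot be blinded and that A-PPTs are masked to the arm for all remaining T1 assessments. If the sponsor holds that A-PPTs must know the arm, give the reason instead and report the limitation.
2. Keep the arm out of the A-PPT's view in Castor and out of the app and email messages that A-PPTs receive. An access setting alone would not close the second route.
3. Ask participants and L-PPTs not to tell the A-PPT which stimulation was given.
4. Where A-PPT and L-PPT are the same person, have another existing A-PPT do the T1 assessment if travel allows.
5. Where that is not possible, and for T1 assessments already done unmasked, record masking status for each participant. Run a sensitivity analysis of the palpation and EMG outcomes without those cases, and compare the estimates and intervals with the full analysis rather than their significance, since the subset may be small.
6. Report unmasked assessment among the limitations in the Discussion, which does not mention it at present.

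The cost is some coordination and an occasional longer journey for a participant. No extra staff, participants or outcomes are needed.

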Regarding attrition, we estimate a loss-to-follow-up of 20 %. Therefore, with 40 participants per group needed in the analysis, 150 participants will be recruited (50 per group).

The primary analysis will use linear mixed models, which accounts for missingness due to study drop-out, under the assumption of missing at random (MAR). Other missing data will be imputed using multiple imputation for intention-to-treat analysis if more than 5 % is missing, with the number of imputations based on the percentage of incomplete patients and relevant variables.

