### Data management and data protection

3.3

After inclusion, all data will be stored in a secure, online database system (www.castoredc.com). Every participant is given a unique identifying trial number. The key to the sequential participant code (a combination of country, institute code, study code and sequential participant number) to the participant data is safeguarded by LUMC.

The handling of the data complies with the EU General Data Protection Regulation and the Dutch Act on Implementation of the General Data Protection Regulation. (in Dutch: Uitvoeringswet AVG, UAVG).

The project leader and PI will have access to the complete database, as well as a monitor of the internal monitor pool of the LUMC and the “Health and Youth Care Inspectorate”.

LUMC data management guidelines will be followed and we strive to make our data FAIR (Findable, Accessible, Interoperable and Reusable) as described in a data management plan.

The data sets will be accessible in agreement with the given informed consents and other agreements in place. Data will be made (publicly) accessible following the funder's guidelines.

The data collected for the trial will consist of baseline characteristics, questionnaires, PFM assessment and EMG assessment (Table 1).

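### Two people analyse the data but only the statistician is stated to be blinded; both analysts should work on coded arms until the analysis decisions are final

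*Protocol article*

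**What the plan says.** All references are to the protocol article.

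- Section 2.6 on participants and therapists: "Participants are blinded for the treatment, but blinding is impossible for the A- and L-PPT's".
- Section 2.6, next sentence, on the analysis: "Data analysis is conducted by both researcher and statistician, with the statistician being fully blinded". It does not say who the researcher is, which analyses each person runs, or what the researcher's blinding status is.
- Section 3.3 on access: "The project leader and PI will have access to the complete database". The allocation field is not mentioned, either as included or as withheld.
- Section 2.5 on the PI's role: "The PI oversees the organization of the project and ensures that the A-PPT and L-PPT receive the required information"; and "Communication between PI, A-PPT's and L-PPT's will be via a secure app and email". On randomisation itself: "The PI has no influence on the randomization process".
- Section 3.2 names a linear mixed model under MAR and Dunnett's closed procedure for the primary comparisons. For the remaining missing values: "Other missing data will be imputed using multiple imputation for intention-to-treat analysis if more than 5 % is missing".

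**The concern.** Blinding the analysis protects decisions taken after the data are in: which queries to raise, which values to correct, whether and how to impute, how to summarise a measure with several readings. It works only if everyone who shares in those decisions is blind. If one of two analysts knows the arms, those decisions can be influenced, even unintentionally, by what they do to the comparison. The blindness of the other analyst does not undo that.

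The point carries more weight here for the secondary outcomes. The assessing therapists (A-PPTs) carry out the palpation and EMG assessment and enter both those data and the bladder diary, and section 2.6 says they cannot be blinded. For these outcomes the analyst's blindness is one of the few safeguards left.

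**Working it through.** No arithmetic applies, because the point does not depend on sample size, power, alpha or effect size. The check sets the statements side by side and asks what each one settles.

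1. **Who analyses, and who is blind (section 2.6).** There are two analysts and one is declared fully blinded. The sentence follows directly on one that sorts the other parties into blinded and not blinded, so singling out the statistician implies a contrast. That is an inference: partial blinding of the researcher, or work on coded arms, would also fit the words.

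2. **Who can see the data (sections 2.5 and 3.3).** Outcome data are held in Castor EDC, and randomisation is done with the same system. The project leader and PI have access to the complete database. Nothing says that allocation is hidden from them, and nothing says that they see it. No statement keeps full-access roles out of the analysis.

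3. **What the randomisation statement covers (section 2.5).** That the PI cannot influence randomisation concerns how allocations are made. It does not address who knows them afterwards, so it does not fill the gap in step 2.

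4. **What is protected regardless.**
   - The IPSS is collected by online questionnaire (section 2.3.1: "Questionnaires (Table 1) will be sent to the participant online at T0, T1 (12 weeks), T2 (24 weeks), and T3 (one year") from participants who are blinded, so no unblinded person scores it.
   - The primary model, the contrasts and the multiplicity procedure are named in section 3.2.
   - A fully blinded statistician takes part in the analysis.
   - Section 3.4 plans no interim analysis, so no comparative look before the end is foreseen.

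5. **What is left exposed.**
   - *Data cleaning.* Both analysts may share in it, and no rule on masked arms is given.
   - *Imputation.* The trigger of more than 5 % is set in advance, but someone has to apply it and choose the variables that enter the imputation. A SAP may fix those details, and their absence from the article is not criticised here. A SAP rule would still be applied by people whose blinding is not stated.
   - *Secondary outcomes.* Sections 2.3 and 2.4 list many palpation, EMG and diary measures, assessed or entered by the unblinded A-PPTs.

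6. **Whether the design needs an unblinded analyst.** With no data safety monitoring board, stopping rules or interim analyses (section 3.4), the article states no reason for an analyst to know the arms before the final analysis.

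**The case against.** The strongest reply is that the article never says the researcher is unblinded, and that a condensed article can leave the division of analysis tasks to the full protocol or SAP. The second half of that is fair for the division of tasks. But section 2.6 does fix a rule on analyst blinding, and as worded the rule covers one analyst of two. If the researcher is in fact blinded, the sentence still needs the same correction.

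A second reply is that the primary result is well guarded. This largely stands: self-report by blinded participants, a named model and a named testing procedure leave limited room to steer the IPSS comparison. It would be wrong to say that blinding the statistician gives no protection.

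Three stronger readings are tempting, and the document does not support them:

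- *The PI knows the allocation, or is the analysing researcher.* Section 3.3 is a data-protection paragraph and does not mention allocation. The information that the PI passes to therapists in section 2.5 is not said to include it. No passage identifies the researcher.
- *IPSS is seen by arm as it accrues.* Section 3.3 gives no timing for access, and no interim comparison is planned.
- *Later allocations can be guessed from the blocks.* Block sizes vary between 6, 9 and 12 within gender strata, the PI's eligibility check comes before consent, and randomisation follows only after the baseline assessment. Guessing would require knowledge of past allocations, the current block size and the order of pending participants, and the article shows none of this. It would in any case be a question of selection bias, separate from analyst blinding.

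**Conclusion.** The concern holds in a limited form. As written, the plan allows a co-analyst who knows the arms to take part in data cleaning, imputation decisions and the secondary analyses, and nothing in the article separates full database access from the analysis. The conclusion rests on reading section 2.6 by contrast, which is the natural reading but not an explicit statement.

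The resulting bias cannot be sized from the document. Qualitatively, the exposure is smaller for the primary IPSS comparison and larger for the pelvic floor muscle, EMG and diary outcomes. This is an inexpensive improvement that should be made. It does not show that the primary result would be invalid.

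**What to change.** In section 2.6, replace the sentence on data analysis with wording to this effect: the researcher and the statistician both work with arms coded A/B/C until data cleaning, the imputation decision and the primary model output are final, and the code is broken only then. Add that anyone who knows the allocation for logistical reasons, including the PI if that applies, takes no part in analysis decisions before the code is broken.

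The cost is a few lines of text and a small organisational burden: someone outside the analysis has to hold the code and handle allocation queries. Treatment, sample size and tests do not change. Recruitment began in September 2023, so the change cannot undo any exposure that has already occurred, but it can be adopted at any time before the analysis starts.
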